### Data management

Data collected for this trial are entered into OpenClinica, a web-based electronic data capture system, and stored on a secure server at the data coordinating center. An automated system for validating data against a set of predefined rules will query clinical centers regarding data that are invalid, illogical, or incomplete. Data elements critical to the primary aim of this trial are monitored remotely by the data coordinating center to confirm the accuracy of entered data compared with the source documents. Remote monitoring is performed on initial subjects enrolled at each clinical center and then on a subset of additional subjects enrolled throughout the trial.

### Statistical analysis

The primary analysis is to assess the effect of the intervention on survival with favorable neurologic outcome. This analysis is based on subjects enrolled during the control period or the intervention period and excludes subjects enrolled during the transition period. Secondary events (after the first eligible CPR event) during the hospitalization are excluded. The effect of the intervention will be assessed with the following test of hypothesis:H_0_: The intervention does not affect the rate of survival with favorable neurologic outcome.H_1_: The intervention increases or decreases the rate of survival with favorable neurologic outcome.

Survival with favorable neurologic outcome will be the outcome for a multivariable logistic regression model. The primary predictor in the model will be treatment group (intervention vs. control). Fixed covariates in the model will be age category (≤ 6 months, > 6 months), Pediatric Risk of Mortality score (PRISM; a measure of illness severity in the 2–6 h prior to CPR) [40], first documented rhythm, illness category (medical cardiac, surgical cardiac, medical noncardiac, surgical noncardiac), and a piecewise linear spline of time. Age, illness category and severity, and first documented rhythm are known predictors of mortality and are included to improve the model fit and potentially increase power. In contrast, survival with favorable neurologic outcome is not expected to change over time. However, without adjusting for time, an improvement over time in survival with favorable neurologic outcome that is unrelated to the intervention would be erroneously interpreted as evidence for the intervention owing to the increased enrollment in the intervention group toward the end of the trial. Including time as a covariate is critical for TSW and HSW designs in order to have valid inference in case of potential temporal trends. Although time is often modeled as a categorical variable in TSW trials, we chose to model time as a piecewise linear spline because we expect it to provide better model fit with fewer estimated parameters. For the spline, knots will divide the enrollment period into epochs of equal duration. The number of knots will be chosen to minimize the Akaike information criterion. There are 18 distinct units at the 10 participating hospitals. Unit will be included as a random effect to account for variability in outcomes between units and increase the generalizability of results.

The data needed for this analysis are readily available, and automated data validation ensures that critical measurements are entered. However, in a very small number of subjects, the window for the PRISM score will be entirely prior to hospitalization. In order to obtain a best estimate of prearrest severity of illness, measurements more than 30 minutes prior to the arrest may be used in this case. In the very rare case that a subject experiences a CPR event within the first 30 minutes of hospitalization, all values will be assumed to be normal prior to the decompensation associated with the CPR event.

This trial compares the effect of the ICU-RESUS intervention to current practice, but participating units had varied quality improvement programs prior to this trial. Although participating units are committed to implementing the ICU-RESUS intervention as scheduled by randomization, they are free to continue, modify, or supplement existing programs with other interventions. The programs in place in each unit will be tracked throughout the trial to allow a description of the control group and an exploratory investigation of additional elements of a successful program.

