### Outcome assessment

As in the single center pilot study, the primary outcome is survival to hospital discharge with favorable neurologic outcome. Neurologic outcome is measured with the Pediatric Cerebral Performance Category scale (PCPC [32]) (Table 1) as per standard Utstein-style reporting guidelines [33]. Survivors are considered to have a favorable neurologic outcome if they have no worse than moderate disability at hospital discharge (PCPC score of 1, 2, or 3) or if their PCPC is no worse than at baseline. Baseline PCPC is retrospectively assessed in enrolled patients and is typically based on their status prior to the event leading to the current hospitalization. However, baseline PCPC is evaluated no more than 30 days prior to CPR for subjects who have been in the hospital for more than 90 days. Subjects who are born during the same hospitalization in which the CPR occurred will have their baseline PCPC assessed based on their status prior to the decompensation associated with the CPR event. PCPC assessment is performed by unblinded research coordinators on the basis of detailed objective criteria [32].

**Table 1 Tab1:** Pediatric Cerebral Performance Category scale

Score	Category	Description
1	Normal	At age-appropriate level; school-age child attend regular school
2	Mild disability	Conscious, alert, able to interact at age-appropriate level; regular school but grades perhaps not age-appropriate, possibility of mild neurologic deficit
3	Moderate disability	Conscious, age-appropriate independent activities of daily living; special education classroom and/or learning deficit present
4	Severe disability	Conscious, dependent on others for daily support because of impaired brain function
5	Coma or vegetative state	Any degree of coma, unaware, even if awake in appearance, without interaction with the environment; no evidence of cortex function; possibility for some reflexive response, spontaneous eye-opening, sleep-wake cycles
6	Brain death/death	Brain death, death

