### Sample size calculation

In the single-center pilot, the intervention was associated with an increase in survival with favorable neurologic outcome from 29% to 50% (21 percentage points). We anticipate that we will see improvement to a rate similar to that achieved in the single-center pilot, but preliminary data from another study show that CPCCRN hospitals have a higher average baseline rate of survival with favorable neurologic outcome than the single-center pilot [34]. Therefore, our goal was to select a design and sample size that would provide approximately 80% power (at a significance level of α = 0.05) to detect a more conservative increase from 40% to 51% in survival with favorable neurologic outcome. An important factor for sample size calculation in cluster-randomized trials is the intracluster correlation (ICC), a measure of the similarity in outcomes among patients in the same cluster compared with outcomes among patients in different clusters [35]. The ICC was assumed to be 3% on the basis of pilot data from the multicenter Therapeutic Hypothermia after Pediatric Cardiac Arrest In-Hospital Trial [36].

The power and sample size estimates used for planning this trial were based on the method introduced by Hussey and Hughes [37], though generalized to allow for transition periods and implemented in PASS version 15 software [38]. This method uses a Wald Z-test to evaluate a null hypothesis of no effect against a two-sided alternative. We considered several trial design configurations, including parallel group, TSW, and HSW designs. We also investigated the impact of transition duration. With an ICC of 3%, an HSW design was found to be optimal (Table 2) [21, 39]. Long transition periods in HSW and especially in TSW designs increased the trial duration necessary to achieve > 80% power (Table 2). Therefore, an HSW design was selected with short (3-month) transitions.

**Table 2 Tab2:** Required duration of enrollment to achieve > 80% power

	Duration of enrollment (years)^a^
Trial design	
Parallel	NA^b^
Traditional stepped-wedge	
6-month transition	6
3-month transition	5.25
Hybrid stepped-wedge	
6-month transition	4.75
3-month transition	4.5

^a^Duration of enrollment is the approximate number of years required to achieve > 80% power to detect an increase from 40% to 51% in the rate of survival with favorable neurologic outcome

^b^In this context, a parallel design cannot achieve 80% power, regardless of the duration of enrollment

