To estimate power for the HSW design, we assume that two hospitals, each with two units, are randomly assigned to begin with the intervention, and similarly that four units at two hospitals are assigned to remain as control hospitals for the duration of the study. Enrollment was assumed to be evenly distributed across the 18 units and also across the 18 time periods. A 3-month transition period was included for each of the ten transitioning units in the design-pattern matrix (Table 3). Units are the clusters used for sample size calculations and planned analyses. However, as noted above, randomization occurs at the hospital level to minimize the possibility of intervention contamination between units within a hospital. We found that analyzing 1256 index events (4 per unit per period) would provide 77% power to detect an 11-percentage-point increase in the rate of survival with favorable neurologic outcome from a baseline rate of 40%. Power increases to 84% when analyzing 1570 index events (5 per unit per period). On the basis of concavity of the power curve, analyzing 1391 subjects provides > 80% power. On the basis of historical CPR rates in participating units, we anticipate enrolling 1540 index events over the 4.5-year enrollment period. An estimated 48 index events will occur during the transition periods, allowing analysis of the remaining 1492 events and providing > 80% power.

**Table 3 Tab3:** Design-pattern matrix for sample size calculations in a 4.5-year hybrid stepped-wedge design with 3-month transitions

Unit	Time period (18 × 3 months)																	
	T1	T2	T3	T4	T5	T6	T7	T8	T9	T10	T11	T12	T13	T14	T15	T16	T17	T18
1	0	0	0	0	0	0	0	0	0	0	0	0	0	0	0	0	0	0
2	0	0	0	0	0	0	0	0	0	0	0	0	0	0	0	0	0	0
3	0	0	0	0	0	0	0	0	0	0	0	0	0	0	0	0	0	0
4	0	0	0	0	0	0	0	0	0	0	0	0	0	0	0	0	0	0
5	0	0	0	0	0	0	0	0	0	0	0	0	0	0	0	.	1	1
6	0	0	0	0	0	0	0	0	0	0	0	0	0	0	0	.	1	1
7	0	0	0	0	0	0	0	0	0	0	0	0	.	1	1	1	1	1
8	0	0	0	0	0	0	0	0	0	0	0	0	.	1	1	1	1	1
9	0	0	0	0	0	0	0	0	0	.	1	1	1	1	1	1	1	1
10	0	0	0	0	0	0	0	0	0	.	1	1	1	1	1	1	1	1
11	0	0	0	0	0	0	.	1	1	1	1	1	1	1	1	1	1	1
12	0	0	0	0	0	0	.	1	1	1	1	1	1	1	1	1	1	1
13	0	0	0	.	1	1	1	1	1	1	1	1	1	1	1	1	1	1
14	0	0	0	.	1	1	1	1	1	1	1	1	1	1	1	1	1	1
15	1	1	1	1	1	1	1	1	1	1	1	1	1	1	1	1	1	1
16	1	1	1	1	1	1	1	1	1	1	1	1	1	1	1	1	1	1
17	1	1	1	1	1	1	1	1	1	1	1	1	1	1	1	1	1	1
18	1	1	1	1	1	1	1	1	1	1	1	1	1	1	1	1	1	1

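### The primary model has no measure of pre-arrest neurologic state, although baseline PCPC is collected and enters the outcome; adding it would be a cheap, modest improvement

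*Protocol article*

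**What the plan says.** The Statistical analysis section of the protocol article specifies a logistic model with treatment group as the main predictor. The adjustment list begins "Fixed covariates in the model will be age category" (cut at 6 months) and continues with PRISM, first documented rhythm, illness category in four classes and a piecewise linear time spline. Unit is a random effect. The patient-level covariates are justified as predictors of mortality that should improve fit and may add power. The list is closed, and the article neither mentions baseline PCPC there nor explains its absence.

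Under Outcome assessment, the primary outcome is survival to discharge with favorable neurologic status. A survivor qualifies with a discharge PCPC of 1, 2 or 3, "or if their PCPC is no worse than at baseline". Baseline PCPC is rated retrospectively in enrolled children, with special reference times for long-stay patients and for infants born during the same admission. PCPC is rated by unblinded coordinators.

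Under Randomization, the permutations were restricted only on expected enrollment. Four of the ten hospitals never cross over.

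**The concern.** The covariates were chosen as predictors of mortality, but the outcome is survival plus a neurologic criterion. PRISM describes acute illness in the hours before CPR, and illness category separates cardiac from noncardiac and medical from surgical. No covariate directly measures neurologic state before the arrest.

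The outcome definition also ties the chance of success to baseline among survivors. A child at baseline 1 can lose two categories and still count as favorable, and a child at baseline 2 can lose one. A child at baseline 3 or worse can lose none. At baseline 5 survival alone suffices, because the only worse category is brain death or death.

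Two things are at stake. A collected prognostic variable that could add power is not used. And with few randomized hospitals and no balancing on case mix, the mix of baseline disability could differ by condition by chance.

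**Working it through.** **1. Inputs from the article (Sample size calculation, Table 3).** Rates are 40% against 51%, a difference of 0.11; two-sided α is 0.05; ICC is 0.03 with unit as the cluster. On the test: "This method uses a Wald Z-test to evaluate a null hypothesis of no effect against a two-sided alternative". On the layout: "A 3-month transition period was included for each of the ten transitioning units in the design-pattern matrix". This leaves 18 × 18 − 10 = 314 analyzed unit-periods.

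**2. Formula.** The Hussey-Hughes model has a categorical period effect and a random unit intercept. Total variance is 0.40 × 0.60 = 0.24, between-unit variance τ² = 0.03 × 0.24 = 0.0072, and within-unit variance σ² = 0.97 × 0.24 = 0.2328. With m = N/314 events per unit-period, the covariance matrix of unit i is V_i = (σ²/m)I + τ²J. The SE of the effect is the square root of the treatment element of (Σ X_i′V_i⁻¹X_i)⁻¹. Power = Φ(0.11/SE − 1.96).

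**3. Reproducing the stated power.** The article says that "analyzing 1256 index events (4 per unit per period) would provide 77% power".

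| Events analyzed | Stated | Recomputed |
|---|---|---|
| 1256 | 77% | 77.3% |
| 1391 | >80% | 80.3% |
| 1492 | >80% | 82.2% |
| 1570 | 84% | 83.6% |

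At 1492 events, m = 1492/314 = 4.75 and SE = 0.0381, so power = Φ(0.11/0.03814 − 1.96) = Φ(0.92) = 82.2%. Other variance conventions fit the stated figures less closely and give 79.8% to 81.5% at 1492 events.

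**4. Effect of adding baseline PCPC on power.** Let R² be the further share of outcome variance that it explains, and replace σ² by σ²(1 − R²). The article gives no R², so these values are assumed.

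| Assumed further R² | SE | Power at 1492 |
|---|---|---|
| 0 | 0.0381 | 82.2% |
| 1% | 0.0380 | 82.5% |
| 3% | 0.0377 | 83.1% |
| 5% | 0.0374 | 83.6% |

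The gain at 5% is 83.6 − 82.2 = 1.4 points. Under the convention that starts at 79.8%, power rises to about 81.2%, a similar gain.

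**5. Is 0-5% a sensible range?** Take one binary term for abnormal baseline, with assumed prevalence q of 10-40%, an assumed residual odds ratio of 0.4-0.8 or 1.5, and an overall favorable rate of 45.5% (midway between 40% and 51%). Then R² = q(1 − q)d²/(0.455 × 0.545), where d is the difference in favorable rate between abnormal and normal baseline. For q = 0.3 and odds ratio 0.4, d = −0.218 and R² = 0.3 × 0.7 × 0.218²/0.248 = 4.0%. Across all the scenarios R² runs from 0.1% to 4.7%.

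**6. Size of a chance imbalance.** The shift in the unadjusted risk difference is the imbalance in prevalence multiplied by d. For an assumed 5-point imbalance and odds ratio 0.8, it is 0.05 × 0.055 = 0.3 points. For a 10-point imbalance and the largest d, it is 0.10 × 0.221 = 2.2 points. The target effect is 11 points and the SE is 3.8 points. The shifts are computed with no adjustment at all, so they lie on the high side for the planned model.

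**The case against.** The strongest reply is that nothing here is an error. The model prespecifies four patient-level covariates, time and a unit effect, with reasons. Omitting a fifth covariate leaves the analysis valid, and that stands.

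A reader might infer more than the article supports, in three ways.

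- **That the trial is underpowered without the covariate.** It is not. The stated power reproduces with no covariate adjustment and exceeds 80% at 1492 events.
- **That the model cannot remove a case-mix difference.** This is too strong. PRISM, illness category, rhythm and age may capture part of it, the unit effect absorbs part of any stable between-unit difference, and the six crossing hospitals contribute within-unit comparisons. The outcome rule also stops survivors with severe baseline disability from failing because of that disability alone.
- **That precision is lost.** In logistic regression an added prognostic covariate can raise power, but it does not shrink the SE of the conditional log odds ratio. The variance scaling in the working is a linear-model approximation.

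The direction of the residual association is also unknown. Severe baseline disability makes the neurologic criterion easier for a survivor but may go with higher mortality.

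A further objection is that a retrospective rating, in a trial whose PCPC assessors are unblinded, could bring assignment-related measurement error into the model. This is a fair caution but a limited one: the same baseline value already enters the outcome, so leaving it out of the covariates does not remove the exposure. It does justify showing the result both ways.

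**Conclusion.** The point holds as a modest improvement to a valid plan. The protocol article fixes a covariate list with no direct measure of pre-arrest neurologic state, although one is collected and helps define success.

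Under an assumed further R² of 0-5%, the power forgone at 1492 events is between nothing and about 1.4 points. Any bias removed is probably small against 11 points. The assumed imbalances give 0.3 to 2.2 points before any adjustment, and the existing covariates and unit effect would take up part of that. These sizes rest on assumed prevalence, association and imbalance, because the article gives none of them. What is firm is the omission, the dependence of each survivor's permitted worsening on baseline, and the reproduced power.

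**What to change.** Prespecify baseline PCPC, for example as 1, 2, 3 and 4-5, as a fixed covariate in the primary model. Settle this before any outcome comparison by group, including the efficacy monitoring that the Data and safety monitoring section places after the second year of enrollment. Adding the term after seeing an imbalance would not be credible. Report the model without baseline PCPC as a sensitivity analysis.

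The cost is an amendment to the analysis text and about three extra parameters, against roughly 600 favorable outcomes even at the 40% rate (1492 × 0.40 = 597). No new data are needed. The remaining downside is reliance on a retrospective rating, which the outcome already uses.

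Modeling age more finely than a single cut at 6 months, which puts everyone from 7 months to 18 years in one class, is optional and secondary.

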### Participants

ICU-RESUS is supported by the National Heart, Lung, and Blood Institute (NHLBI) and conducted by the *Eunice Kennedy Shriver* National Institute of Child Health and Human Development-funded Collaborative Pediatric Critical Care Research Network (CPCCRN). Hospitals were eligible for participation if they had not implemented either of the elements of the ICU-RESUS intervention and were committed to not implementing the intervention until scheduled by the trial randomization. The ten participating hospitals are geographically diverse tertiary care pediatric hospitals with patients from a mixture of urban, suburban, and rural areas of the United States [31]. These hospitals include 18 distinct units from which subjects will be enrolled.

All eligible subjects at participating institutions are enrolled under a waiver of consent. The central institutional review board at the University of Utah granted a waiver of consent based on the following factors:ICU-RESUS poses no more than minimal risk, because CPR training already exists in the ICUs and resuscitation quality should be at least as good with the ICU-RESUS intervention.The study involves no therapeutic intervention at the patient level, because the intervention is targeted to the care environment and does not deviate from accepted clinical practice.Obtaining informed consent would threaten the scientific validity of the study, which depends on capturing all eligible events during the enrollment period.

Subjects are considered for eligibility if they (1) are ≥ 37 weeks gestational age and ≤ 18 years of age and (2) receive CPR in the ICU. Subjects are excluded if they, prior to the arrest, (1) had a preexisting terminal illness and were not expected to survive the hospitalization (e.g., patients transferred to the ICU for end-of-life care); (2) had a lack of commitment to aggressive ICU therapies; (3) were brain dead; or (4) had an out-of-hospital cardiac arrest associated with the current hospitalization. CPR events lasting < 1 minute will be excluded from analysis if a site investigator determines CPR to have been unnecessary.

We anticipate enrolling 1540 index CPR events from 18 clinical units at 10 participating hospitals during a 4.5-year enrollment period. A schedule of enrollment, interventions, and assessment is provided in Fig. 2.

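### The primary model reduces age to a single cut at 6 months in a trial enrolling up to 18 years; unless the age effect is a step there, some prognostic information is lost, at a small cost in power.

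*Protocol article*

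**What the plan says.** In the Statistical analysis section, the primary analysis is a multivariable logistic regression of survival with favorable neurologic outcome on treatment group, with unit as a random effect. Age enters as two groups, at most 6 months and over 6 months: "Fixed covariates in the model will be age category". The other covariates are PRISM, first documented rhythm, a four-level illness category and a piecewise linear spline of time. Age, illness category, severity and rhythm are described as known predictors of mortality that "are included to improve the model fit and potentially increase power".

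The Participants section admits children from 37 weeks gestational age up to "18 years of age and (2) receive CPR in the ICU". The upper age group therefore runs from just over 6 months to 18 years.

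The Sample size calculation section describes no adjustment for age or any other baseline covariate. The article gives no age distribution, no age-outcome relation and no reason for the 6-month cut.

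**The concern.** A two-level term can carry only one contrast. Any gradient in outcome among children over 6 months, or within the first 6 months, is invisible to it. The stated purpose of the covariate is fit and power, so the coding works against that purpose unless the true relation is close to a step at 6 months. The same section gives calendar time, for which no trend is expected, a flexible spline partly on grounds of fit. The time spline also protects validity, so the parallel is not exact, but the fit argument applies equally to a known predictor.

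Two things are at stake. One is a little power. The other is adjustment: only ten hospitals are randomised, and the Randomization section describes balancing on expected enrollment only. Differences in age mix between hospitals or over time are left to the model, and those within the over-6-month group bypass the age term. The article gives no figure from which to size such an imbalance.

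**Working it through.** **1. Inputs.** From the Sample size calculation section:

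- a target of "approximately 80% power (at a significance level of α = 0.05");
- an "increase from 40% to 51% in survival with favorable neurologic outcome";
- "The ICC was assumed to be 3"%;
- "This method uses a Wald Z-test to evaluate a null hypothesis of no effect against a two-sided alternative";
- the matrix in Table 3, with 18 × 18 = 324 cells less 10 transition cells = 314 analysed cells (162 control, 152 intervention);
- 1492 events expected in the analysis.

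Assumptions, because the article gives no values: the share of children at or below 6 months, the shape of the age effect, and the fraction R² of residual variance that age explains (1–10%).

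**2. Reproducing the plan's power.** This uses the Hussey-Hughes generalised least squares variance on Table 3, with categorical periods, a random unit intercept and transition cells dropped. Total variance is 0.4 × 0.6 = 0.24, between-unit variance 0.03 × 0.24 and within-unit variance 0.97 × 0.24. Power = Φ(0.11/SE − 1.96).

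| Events | Stated | Recomputed |
|---|---|---|
| 1256 | 77% | 77.3% |
| 1391 | > 80% | 80.3% |
| 1492 | > 80% | 82.2% |
| 1570 | 84% | 83.6% |

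The plan's figures reproduce, and no age term enters them.

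**3. Information kept by the cut.** The loss is 1 − (squared correlation of the 6-month indicator with the true age function). For a normally distributed covariate with a linear effect and share q below the cut point c, this is

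loss = 1 − φ(c)² / [q(1 − q)].

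At q = 0.5: 1 − 0.3989²/0.25 = 36.3%. At q = 0.4 it is 37.8%, at 0.3 it is 42.4%, at 0.2 it is 51.0% and at 0.1 it is 65.8%.

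For skewed ages (log-normal, truncated at 18 years, 30–50% at or below 6 months), the loss by shape is:

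| True age effect | Loss |
|---|---|
| Step at 6 months | 0% |
| Fading over the first 6–12 months of life | 18–27% |
| Linear in log age | 35–37% |
| Threshold at 1 year | 48–53% |
| Linear in years | 75–79% |

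**4. What this is worth in power, linear approximation.** At 1492 events (82.2% with no age term), the within-unit variance is multiplied by 1 − R² for a correctly specified age term, and by 1 − R²(1 − loss) for the cut.

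| R² of age | Loss | Full term | Cut | Difference (points) |
|---|---|---|---|---|
| 1% | 36% | 82.5% | 82.4% | 0.1 |
| 2% | 36% | 82.8% | 82.6% | 0.2 |
| 5% | 36% | 83.6% | 83.1% | 0.5 |
| 10% | 36% | 85.0% | 84.0% | 1.0 |
| 5% | 75% | 83.6% | 82.6% | 1.0 |
| 10% | 75% | 85.0% | 82.9% | 2.1 |

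The last row combines the largest assumed R² with an effect close to linear in years.

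**5. The mechanism in a logistic model.** The planned model is logistic and has no residual variance to reduce, so step 4 only approximates size. A simplified simulation checks the direction: individual randomisation, no clustering, 1492 children, 45% at or below 6 months, ages spread evenly in log age from 1 day within each group, 40% versus 51%. Replacing the indicator with linear log age gives:

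| Log-odds per doubling of age | Mean SE of treatment log odds ratio | Mean z |
|---|---|---|
| 0.10 | 0.1061 → 0.1065 | 4.18 → 4.20 |
| 0.20 | 0.1095 → 0.1111 | 3.98 → 4.04 |

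The standard error rises slightly, but the estimate moves further from zero by more, so z rises. In a further unclustered simulation with mean z near the 80% power point, the standard error went from 0.1071 to 0.1081 and mean z from 2.80 to 2.82. In power, that is Φ(2.80 − 1.96) = Φ(0.84) = 80.0% against Φ(0.86) = 80.5%, about half a point. Across the shapes tried there, including a true step and no age effect, the spline cost essentially nothing and gained at most about one point.

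**The case against.** The strongest case for the plan is that this is a prespecified coding, that no figure depends on it, and that the gain from changing it is of the order of one point of power or less. All of that stands. The calculation in step 4 also credits age with its full R², although PRISM, rhythm and illness category are already in the model and may share part of it, so the gain could be smaller still. Unit effects and the time spline absorb some case-mix difference.

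A cut at 6 months would also be a reasonable choice if the age effect is concentrated in early infancy. The article does not argue this, but nothing in it rules it out.

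A reader might infer two stronger things. The first is that the cut discards at least a third of age's information. That figure holds for an effect linear in log age; it is not a floor, because the loss is 18–27% for an early-infancy effect and nil for a step, and the article has no data to choose between them. The second is that the cut widens the confidence interval. For the log odds ratio in a logistic model the direction is the opposite: better adjustment slightly raises the standard error, and the power comes from the larger conditional estimate.

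Finally, the article does not say in what form age is recorded. Applying the eligibility limits and the 6-month cut requires each child's age, so needing no new data is a fair inference but still an inference.

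**Conclusion.** The point holds as a minor efficiency improvement. The primary model treats all children from just over 6 months to 18 years alike on a covariate included for fit and power. Unless the true effect is a step at 6 months, part of age's prognostic information is lost; how much depends on a shape and an age distribution that the article does not give. The likely cost is roughly 0 to 1 point of power, with 2.1 points only in the extreme corner of the assumed range. Some age case-mix differences among children over 6 months also stay outside the age term, by an amount that cannot be sized from the article. The planned power above 80% is unaffected and nothing stated in the plan is numerically wrong. The power figures rest on a linear approximation and on unclustered simulations, so they indicate order of magnitude only.

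**What to change.** In the primary logistic model, replace the two-level age category with a restricted cubic spline of log(age + a small fixed offset, for example 1 week), with 3 degrees of freedom and knots fixed in advance at stated quantiles of age. The offset is needed because newborns are eligible: the logarithm is undefined at age 0 and exaggerates differences of a few days. Keep the 6-month grouping for descriptive tables.

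The cost is two extra parameters among about 1492 events. The spline can follow an early-infancy effect as well as later gradients, so it does not require knowing the shape beforehand. The change should be made without reference to outcome data by group.
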